### Randomization

Participants will be randomized to either the intervention or control group. Each participant will be allocated a number 1 or 2 with equal probabilities using Java’s built-in random number generator (java.util.Random). Randomization is thus fully computerized, does not use any strata or blocks, and is not possible to subvert because this and all subsequent study processes are fully automated.

### Statistical Methods

All analyses will be done under the intention-to-treat principle, where all randomized individuals will be included. Missing outcome data will initially be handled by a complete-case analysis, which assumes that data are missing at random. If data are systematically missing, then it may be the case that early responders differ from late responders, and in extension that late responders are more similar to nonresponders. We will, therefore, explore the plausibility of the missing at random assumption by regressing the primary outcomes on the number of follow-up attempts needed before a response was recorded. To further explore the missing at random assumption, attrition will be investigated among study groups by comparing baseline characteristics between those who did and did not respond at follow-up.

For all models, coefficients of interest will be assessed for statistical significance using a null hypothesis testing approach, where tests will be 2-tailed at the .05 significance level. Alongside the null hypothesis tests, posterior distributions using a Bayesian approach will be calculated for each coefficient. Both significance tests and posterior distributions will create a basis for scientific inference [34].

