### Objectives

This protocol describes a randomized controlled trial that aims to test the efficacy of a fully automated mobile phone–based intervention on positive mental health among university students. The primary hypothesis is that participants in the intervention group will report significantly higher positive mental health (measured by the primary outcome measure) at follow-up compared with participants in the control group. Secondary hypotheses are that the intervention group will report significantly higher emotional, social, and psychological well-being as well as significantly lower rates of anxiety and depression symptomatology (measured by primary and secondary outcomes) at follow-ups compared with participants in the control group. These hypotheses are proposed at 3-, 6-, and 12-month follow-ups. Positive emotions and thoughts are hypothesized to mediate the relationship between access to the intervention and outcomes.

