### Outcomes and Measures

A baseline questionnaire will investigate demographic data (age, gender, and social status), primary outcome [2], and secondary outcomes [29]. Follow-up questionnaires will investigate primary and secondary outcomes. Outcomes will be investigated at baseline and at 3, 6, and 12 months after randomization. Participants will receive and complete questionnaires through their mobile phones.

Primary outcome will be positive mental health, assessed with the 14-item Mental Health Continuum Short Form (MHC-SF) [2]. Higher scores indicate greater emotional, social, and psychological well-being (range 0-84). Secondary outcomes will be depression and anxiety symptomatology assessed as the score on corresponding subscales of the Hospital Anxiety Depression Scale (HADS) [29].

To investigate mediators of the intervention [20], 2 face-valid items will measure the frequency of positive thoughts (‘‘During the last week, to what extent have you experienced positive thoughts” and “During the last week, to what extent have you experienced positive emotions”). Items will be rated on a scale ranging from 0= *not at all* to 9= *to a very high extent*. Mediators are assessed at baseline, midintervention (end of week 5), and at subsequent follow-ups. Mediation scores are hypothesized to be significantly higher in the intervention group compared with the control group.

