### Sample Size

A power analysis was conducted to determine the necessary number of participants to invite to the study. To detect a standardized effect size of 0.3, so as to have the average score in the intervention group exceeding the scores of 62% of the control group, a total of 352 participants are required. The calculations were done assuming an 80% chance of detecting the difference at a significance level of .05 (2-tailed). Assuming that 70% of the participants respond to the follow-up questionnaire, it is necessary to recruit 503 participants in total. Furthermore, assuming that 1% of the invited population is willing to join the study (and are not excluded), we need to invite 50,300 participants.

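### Complete-case analysis does not deliver the promised all-randomised analysis, and it needs a narrower assumption than missing at random, so the 6- and 12-month effects can be biased even if MAR holds

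*Protocol article*

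**What the plan says.** All references are to the protocol article.

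- **Population** (Statistical Methods): "All analyses will be done under the intention-to-treat principle, where all randomized individuals will be included".
- **Missing outcomes** (Statistical Methods, next sentence): "Missing outcome data will initially be handled by a complete-case analysis, which assumes that data are missing at random".
- **Checks on that assumption** (Statistical Methods): one is "regressing the primary outcomes on the number of follow-up attempts needed before a response was recorded"; the other is "comparing baseline characteristics between those who did and did not respond at follow-up". The text attaches no consequence to either result.
- **Models** (Statistical Methods): MHC-SF total is regressed on group by negative binomial regression, unadjusted and adjusted. The adjustment set is demographics, baseline MHC-SF and baseline mediators. The adjusted version is primary. No repeated-measures model is described.
- **Timing**: "Outcomes will be investigated at baseline and at 3, 6, and 12 months after randomization" (Outcomes and Measures), and "These hypotheses are proposed at 3-, 6-, and 12-month follow-ups" (Objectives). The two mediator items are also collected at the end of week 5.
- **Expected response** (Sample Size): "Assuming that 70% of the participants respond to the follow-up questionnaire". The total is raised from 352 to 503 on that basis.
- **Blinding** (Recruitment): participants are aware of their allocation.

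**The concern.** There are two separate problems.

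The first is textual. A regression on complete cases cannot contain a person whose outcome is missing, so "where all randomized individuals will be included" is not met by the method named in the following sentence.

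The second is technical. Complete-case regression with a missing outcome is valid when missingness is unrelated to that outcome given the covariates in the model. For the primary adjusted model this means given arm and baseline. For the unadjusted model it means given arm alone. MAR is wider: it also lets 12-month missingness depend on an observed 3- or 6-month score, or on the week-5 mediator items. The trial collects all of these, but the outcome models omit them. The stated assumption can therefore hold while the primary estimate is biased.

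Arm-different dropout is possible here. Allocation is known, outcomes are self-reported by phone, and only one arm receives a ten-week programme averaging one message a day. At stake is whether a 6- or 12-month difference reflects the programme or who chose to answer.

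**Working it through.** **Step 1. Reproduce the plan's figures.** Inputs from Sample Size: effect 0.3 SD, 80% power, two-sided 0.05, equal allocation, 70% response.

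- The exact two-sample t-test needs 176 per arm, so 2 × 176 = 352. This matches.
- 352 / 0.70 = 502.9, so 503. This matches.
- Left out of a complete-case analysis at that response: 503 × 0.30 = 150.9, about 151.

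**Step 2. Compare the assumptions.**

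| Analysis | Missingness may depend on |
|---|---|
| Unadjusted complete-case | arm |
| Adjusted complete-case (primary) | arm, baseline covariates |
| MAR, given all data collected | arm, baseline, week-5 mediators, earlier observed follow-up scores |

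The protocol assigns the last row's assumption to the first two rows' methods.

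**Step 3. Illustrate the size of the gap.** The documents give no dropout slopes or correlations, so these inputs are assumed:

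- baseline, 3-month and 12-month scores are normal with SD 1 and pairwise correlation 0.6;
- the true effect is 0.30 SD at 3 and 12 months;
- 12-month response is 70% in each arm;
- logit P(response at 12 months) = a + b × (observed 3-month score), where b is set by arm and a is solved to give 70%.

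This mechanism is MAR. The analysis is linear regression of the 12-month score on arm and baseline among responders, in very large simulated samples. A normal model stands in for the negative binomial.

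| Slope b, intervention / control | Adjusted complete-case estimate (truth 0.30) |
|---|---|
| +0.5 / +0.5 | 0.30 |
| −0.5 / −0.5 | 0.30 |
| +0.5 / 0 | about 0.33 |
| −0.5 / 0 | about 0.26 |
| +0.5 / −0.5 | about 0.37 |
| −0.5 / +0.5 | about 0.23 |
| +0.5 / −0.5, but on baseline instead of the 3-month score | 0.30 |

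Imputing the 12-month score by arm from baseline and the 3-month score gives 0.30 in every row, to rounding.

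**Step 4. Vary the assumptions.** With steeper slopes of 1.0 and correlations from 0.5 to 0.7, the adjusted estimate is 0.35 to 0.37 or 0.23 to 0.25 when one arm is affected. It is 0.41 to 0.43 when the arms run in opposite directions (the one ordering run at this slope). With slopes of zero there is no bias.

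**Step 5. Scale the bias against precision.** With 352 responders and correlation 0.6, the standard error of the adjusted difference is about 2 × √(1 − 0.36) / √352 = 0.085 SD. A bias of 0.03 to 0.04 is under half a standard error; 0.07 is about 0.8. If the true effect is zero and the slopes are +0.5 / −0.5, the estimate is about 0.07. Two-sided rejection is then Φ(0.07/0.085 − 1.96) + Φ(−0.07/0.085 − 1.96), about 13% instead of 5%.

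**Step 6. Ask whether the stated checks would detect this.** Number of contact attempts is used as a proxy for nonresponse related to the outcome itself. The baseline comparison looks at baseline variables. Neither relates 6- or 12-month missingness to an earlier follow-up score.

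**The case against.** The case for the plan has real force.

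- **The adjusted model is primary, and baseline is complete before randomisation.** Only the outcome can be missing. If MAR is read as conditional on the model's own covariates, the sentence is right for the primary model. Baseline-driven dropout leaves the adjusted estimate at 0.30 even with opposite slopes by arm. This stands, and it limits the problem to post-baseline dependence. It does not save the sentence as written, because the article does not state that condition and applies the same claim to the unadjusted models.
- **The bias needs arm-different dropout.** This also stands. Equal dependence in both arms gives essentially none, and no passage gives evidence of a difference.
- **Intention-to-treat is often used to mean analysed as randomised, and the trial is sized for 352 responders.** Power is protected and the exclusion is foreseen. But the article goes further and says that everyone randomised is included, so the wording still has to be reconciled.
- **The article signals further work.** The word 'initially' and the two checks point beyond complete-case analysis, and a fuller plan may name the next step. Its absence from an article is not the fault raised here. The fault is that the method and assumption the article does state do not match each other or the population sentence.

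Stronger readings are tempting. A reader might infer that 30% will be lost at every visit, but the 70% is given for the follow-up questionnaire and not per visit; analysis visit by visit is itself inferred from the hypotheses and the absence of a repeated-measures model. A reader might also cite the unadjusted model, where the +0.5 / 0 and +0.5 / −0.5 scenarios give about 0.39 and 0.47. Those describe an analysis that the protocol does not treat as primary.

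**Conclusion.** The point holds as a should-fix. The population sentence and the named method contradict each other, by about 151 of 503 participants at the planned response. The MAR statement is broader than the primary adjusted model supports, and broader still for the unadjusted one.

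Bias in the primary model is possible, not shown. It arises if 6- or 12-month dropout depends on observed post-baseline data differently by arm, and it can go either way: roughly 0.03 to 0.07 SD against a true 0.30 under slopes of 0.5 and correlations of 0.6, more under steeper slopes, and none under equal or baseline-only dependence. The slopes, correlations and normal working model are assumptions.

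A reader might infer that the trial will overstate its effect or that its results will be invalid. The documents support neither. At 3 months there is no earlier follow-up MHC-SF score; the only intermediate data are the two week-5 items, and no 3-month bias has been quantified.

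**What to change.** Make the primary analysis one that uses all observed follow-up data under MAR. Either option would do:

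1. A longitudinal likelihood model for 3, 6 and 12 months with group-by-visit terms and the planned baseline covariates.
2. Multiple imputation by arm from baseline, the week-5 mediators and all observed follow-up scores, followed by the planned adjusted regression at each visit.

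Keep complete-case analysis as a sensitivity analysis, and retain the two existing checks. Add a comparison of 6- and 12-month responders and nonresponders on earlier follow-up scores, by arm.

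Reword Statistical Methods in two places. State that complete-case analysis requires missingness to be unrelated to the outcome given arm and the covariates in the model. Reconcile the intention-to-treat sentence with the chosen method. Under option 1 with baseline as a covariate, people with no follow-up at all still do not enter the likelihood, and the text should say so; option 2 includes everyone randomised.

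The cost is a change of wording and a little more analysis work. The data needed are already collected, and the sample size of 503 does not change.

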**Figure 1 figure1:**
[figure not shown]
Flowchart of the recruitment procedure.

The primary outcome (MHC-SF total score) is a discrete measure, which may be skewed; thus, we will regress this outcome on group allocation using negative binomial regression. Both unadjusted and adjusted models will be explored (adjusting for demographics, total MHC-SF, and mediator variables at baseline).

The 3 subscales of MHC-SF (emotional well-being, social well-being, and psychological well-being) are mean scores from Likert scale items, which should, because of the law of large numbers, tend toward normality. If by visual inspection it is deemed that the measures are skewed, we will use log transformation. We will regress the individual scores against group allocation using normal linear regression. Both unadjusted and adjusted models will be explored (adjusting for demographics and each score, respectively, and mediator variables at baseline).

Depression and anxiety scores from HADS will also be regressed against group allocation using negative binomial regression. Both unadjusted and adjusted models will be explored (adjusting for demographics, depression, and anxiety, respectively, and mediator variables at baseline).

Mediators will be explored using a causal inference framework, where Monte Carlo methods are relied upon for inference. A total of 3 models will be created for each outcome measure: 2 that investigate the mediating factors on their own and a third model that incorporates all mediators at once.

Effect modification tests will be performed in all models to assess if any of the baseline characteristics moderate the effect of the intervention. Adjusted models will be primary.

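### Negative binomial regression is poorly justified for the bounded MHC-SF total: the estimate is not on the scale used for sizing, and model-based standard errors can be too wide.

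*Protocol article*

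**What the plan says.** Under Outcomes and Measures, the primary outcome is positive mental health, "assessed with the 14-item Mental Health Continuum Short Form (MHC-SF"), and the scale is bounded: "Higher scores indicate greater emotional, social, and psychological well-being (range 0-84").

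Under Statistical Methods, the total is called a discrete measure "which may be skewed; thus, we will regress this outcome on group allocation using negative binomial regression". The adjusted version adds covariates ("adjusting for demographics, total MHC-SF, and mediator variables at baseline"), and "Adjusted models will be primary". For the three subscales, formed from the same items, the same section argues that item averages tend toward normality and states: "We will regress the individual scores against group allocation using normal linear regression". No link function or variance estimator is named for the negative binomial model.

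Under Sample Size, the calculation is made "To detect a standardized effect size of 0.3", explained as "so as to have the average score in the intervention group exceeding the scores of 62% of the control group". No mean, SD, ratio or dispersion is given.

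**The concern.** The stated reason does not lead to the chosen model. Negative binomial regression describes counts with no upper limit, right skew, and a variance that exceeds the mean and grows with it. A questionnaire total capped at 84 has a variance that must shrink near the cap. If scores lie mostly above the midpoint of 42, any skew is likely to be to the left.

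The choice also conflicts with the subscale analysis. If averaging a few items justifies a normal linear model, summing all 14 justifies it at least as well. The article gives no reason for treating the total differently.

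Two consequences are at stake for the primary analysis. The effect would be reported as a ratio and could not be set directly beside the 0.3 used for sizing. And adjusting for baseline MHC-SF lowers the residual variance, possibly below the minimum that the model allows, which would make model-based intervals too wide.

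**Working it through.** **1. The plan's own figures.** Inputs from Sample Size: effect 0.3, power 80%, two-sided 0.05, 70% response.
- Normal approximation: 2 × (1.960 + 0.842)² / 0.3² = 174.4, so 175 per arm and 350 in total. The two-sample t-test needs 175.4, so 176 per arm and **352** in total.
- 352 / 0.70 = 502.9, so **503**.
- Φ(0.3) = 0.618, the stated **62%**.

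All three reproduce. They come from a comparison of two means with a common SD, not from a ratio.

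**2. What 0.3 is as a ratio.** Ratio = 1 + 0.3 × SD / mean. The article gives neither quantity, so these are assumptions: means 40-55 and SDs 8-14. The difference runs from 0.3 × 8 = 2.4 to 0.3 × 14 = 4.2 points. The ratio runs from 1 + 2.4/55 = 1.04 to 1 + 4.2/40 = 1.105, about 1.11. The design effect therefore fixes no single ratio.

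**3. The variance floor.** The model variance is μ + μ²/θ, which is never below μ. With baseline correlation r, the residual SD is SD × √(1 − r²). The approximate factor by which the model-based standard error is too wide is max(1, √mean / residual SD), and the type I error is 2 × [1 − Φ(1.96 × factor)]. All values of mean, SD and r are assumed.

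| Mean | SD | r | Residual SD | √mean | Factor | Type I error |
|---|---|---|---|---|---|---|
| 60 | 10 | 0.8 | 6.00 | 7.75 | 1.29 | 0.011 |
| 50 | 10 | 0.8 | 6.00 | 7.07 | 1.18 | 0.021 |
| 50 | 10 | 0.7 | 7.14 | 7.07 | 1.00 | 0.050 |
| 55 | 12 | 0.6 | 9.60 | 7.42 | 1.00 | 0.050 |
| 45 | 12 | 0.8 | 7.20 | 6.71 | 1.00 | 0.050 |
| 50 | 8 | 0.7 | 5.71 | 7.07 | 1.24 | 0.015 |

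The threshold is √50 = 7.1 to √60 = 7.7, so about 7 to 8 points.

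**4. Simulation check.** Scores were bounded at 0-84 and beta-shaped, with 352 participants retained after excluding baseline scores of 70 or more.
- Mean 60, SD 10, r 0.8: separate runs put the standard error 18-33% too wide, with type I error between 1.3% and about 2%. Robust linear regression gave 5.0%.
- Mean 50, SD 10, r 0.7, and mean 55, SD 12, r 0.6: standard errors essentially correct.
- Outcome skew was to the left in the settings where it was examined (about −0.2 to −0.6). This follows from the assumed beta shape with means above 42.

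**5. Power at the planned effect of 0.3, n = 352** (400 runs per setting):

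| Mean | SD | r | Negative binomial | Linear |
|---|---|---|---|---|
| 60 | 10 | 0.8 | 98.8% | 99.8% |
| 60 | 10 | 0.7 | 96.5% | 97.8% |
| 55 | 12 | 0.6 | 93.0% | 92.8% |
| 45 | 14 | 0.6 | 92.5% | 94.0% |

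The largest gap is 94.0 − 92.5 = 1.5 points. With a smaller SD of 8, the step 3 approximation gives more: 0.935 against 0.976 at mean 50, r 0.7, and 0.919 against 0.976 at mean 55, r 0.7. In all these cases power stays well above 80%, because baseline adjustment adds more than the wide standard error removes.

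**The case against.** **The sizing is not invalidated.** A ratio of 1 and a difference of 0 are the same null hypothesis, planning on a standardized effect and then fitting a generalized linear model is common, and fitted means turn a ratio back into points. This stands. The loss is direct comparability with the design effect, nothing more.

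**The standard-error problem is conditional and conservative.** It needs a small SD or a strong baseline correlation, and the article gives neither. A correlation of 0.8 over 3 to 12 months is at the adverse end. Where the problem occurs, it makes a false claim of benefit less likely. This also stands.

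**The article is condensed.** A full analysis plan might specify robust standard errors, and the article also bases inference on Bayesian posteriors. The width criticism therefore applies only to model-based errors. A posterior from the same negative binomial likelihood would carry the same variance floor. The model itself and the reason for it are stated choices, not omitted detail, so that part of the point is unaffected.

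A reader might infer that the trial is underpowered or its sample size wrong. The documents do not support this: 352 and 503 reproduce, and power at 0.3 exceeded 92% in every simulated setting.

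**Conclusion.** The point holds as a weak and internally inconsistent choice of primary model. Three parts rest on the text alone, apart from the assumption of the usual log link: the outcome is bounded, the reason given does not support a count model, and the ratio is not directly comparable with the standardized difference of 0.3.

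The effect on standard errors depends on quantities that the article does not give and on the use of model-based errors. Under assumed values at n=352, it ranges from negligible (mean 50, SD 10, r 0.7; mean 55, SD 12, r 0.6) to about 20-30% too wide with type I error about 2% (mean 60, SD 10, r 0.8). At the planned effect, the power loss was about 2 points or less in the simulated settings with SD 10 to 14. This is neither a power failure nor a route to false-positive findings, but it is worth correcting because it concerns the primary analysis and the remedy is cheap.

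**What to change.** Make the primary model a linear regression of the follow-up MHC-SF total on allocation, adjusted for baseline MHC-SF and the other covariates already listed, with robust standard errors. Report the adjusted mean difference in points and in SD units, naming the SD used, so that it can be set beside 0.3. Keep negative binomial regression, also with robust standard errors, as a sensitivity analysis.

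This brings the total into line with the subscale analysis and with the sizing. It costs a change of analysis wording, best made before outcome data are examined. Data collection, 352 and 503 are unchanged.

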## Introduction

### Background

Mental well-being has traditionally been perceived as simply the absence of mental illness [1]. There is now evidence that positive mental health and mental illness are 2, albeit connected, unique dimensions of mental health. Positive experiences such as personal growth or feelings of hope can occur alongside mental illness. Similarly, the absence of mental illness does not mean automatic presence of positive mental health. Indeed, people afflicted by mental illness can have experiences of personal growth and feelings of hope, indicating that well-being and mental illness are not mutually exclusive [1-5].

Strong positive mental health is associated with various benefits including decreased risk of disease [6-10], decreased risk of mental illness [11-14], and increased longevity [8,15]. In a cohort study, individuals with poor positive mental health were 7 times more likely to be depressed 10 years later [14]. Individuals with poor positive mental health score similar to, or worse than, clinically depressed individuals on outcomes such as everyday functioning (eg, number of days absent from work) and psychosocial functioning (eg, achieving goals) [16]. The promotion of positive mental health among the general population has, therefore, recently been emphasized as the most important goal for the public mental health agenda in Europe [17].

Positive psychology interventions (PPIs) aim to promote positive mental health [18,19]. For example, a brief exercise where the individual is asked “to think about three things that went well during the day and savor those moments” have shown to increase positive mental health [9,19]. The positivity-activity model proposes that PPIs affect the relationship between positive practice (eg, acts of kindness) and well-being through increased positive emotions, thoughts, and behaviors. Furthermore, that features of positive practices (eg, how often do you perform acts of kindness) and individual factors (eg, motivation to be kind) moderate the relationship between positive practice and well-being [20].

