### Recruitment

Students from 11 universities in Sweden will be invited to take part. Recruitment will last for 6 months and be executed by digital advertising (email, university websites, Student Health Services websites, and learning management systems used by the universities). The universities are located throughout Sweden in rural and urban settings. Faculties from medical, technical, art, and social sciences will be represented. The advertisement will include information on the study aims, confidentiality, and trial design. Students will register their interest by sending an SMS text message to a dedicated telephone number (included in the advertisement material). Informed consent and the baseline questionnaire will be completed on their mobile phone. After completing the baseline questionnaire, students will then automatically be randomized to either an intervention or control group. Participants will know that they have been randomized to either an intervention or control group. Figure 1 depicts a flowchart of the recruitment procedure of the study.

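### The primary adjusted models omit the other mental-health scale's baseline score, which is held for everyone; adding it costs almost nothing and guards against arm-dependent dropout

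*Protocol article*

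**What the plan says.** The covariates are listed outcome by outcome in the Statistical Methods section of the protocol article (the text continues below the Figure 1 caption).

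- MHC-SF total: "Both unadjusted and adjusted models will be explored (adjusting for demographics, total MHC-SF, and mediator variables at baseline".
- MHC-SF subscales: "adjusting for demographics and each score, respectively, and mediator variables at baseline".
- HADS depression and anxiety: "adjusting for demographics, depression, and anxiety, respectively, and mediator variables at baseline".

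The section closes its account of the models with "Adjusted models will be primary".

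Both scales are available at baseline. Outcomes and Measures says: "A baseline questionnaire will investigate demographic data (age, gender, and social status), primary outcome [2], and secondary outcomes [29". Recruitment says: "After completing the baseline questionnaire, students will then automatically be randomized to either an intervention or control group". No randomised participant should therefore lack either score.

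Three other statements bear on the point. Missing outcomes are at first handled by complete-case analysis (Statistical Methods). The sample size assumes that 70% respond at follow-up (Sample Size). Participants know which arm they are in (Recruitment; Control Group).

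**The concern.** The Background treats well-being and mental illness as related but distinct dimensions. On that premise, each baseline scale may carry information about the other outcome that the outcome's own baseline does not. The lists do not use it.

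Two things could be lost. One is precision, if the omitted score explains outcome variance beyond the listed covariates. The other is protection against selective dropout. A complete-case regression removes the effect of baseline-related dropout for variables in the model. For a variable left out, the arm contrast is exposed if that variable predicts outcome given the listed covariates and also relates to response differently by arm. Such a difference is conceivable here: allocation is open, and only the intervention arm receives about one message a day for 10 weeks. The plan will compare responders with non-responders on baseline characteristics, but the article names no step that would follow if they differed on HADS.

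**Working it through.** **1. The plan's own figures.** A two-sample t-test with effect 0.3, 80% power and two-sided 0.05 needs 175.4, so 176 per arm and 352 in total. Then 352 / 0.70 = 502.9, so 503. Both figures reproduce, use no covariates, and are unaffected by this point.

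**2. Precision.** The protocol gives no correlations, so these are assumptions: baseline MHC-SF with outcome (r_yb) 0.5 to 0.7; baseline HADS with baseline MHC-SF (r_bh) -0.5 to -0.7; baseline HADS with outcome (r_yh) -0.3 to -0.5. The share of residual variance removed by adding HADS to a model with baseline MHC-SF is

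(r_yh - r_yb × r_bh)² / [(1 - r_yb²)(1 - r_bh²)].

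With 176 per arm, power = Φ(0.3 / (σ√(2/176)) - 1.96), where σ² is the residual variance.

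| r_yb, r_bh, r_yh | Variance removed | Power without → with HADS |
|---|---|---|
| 0.5, -0.6, -0.4 | 0.01 / 0.48 = 2.1% | 90.1% → 90.7% |
| 0.6, -0.5, -0.4 | 0.01 / 0.48 = 2.1% | 94.0% → 94.5% |
| 0.5, -0.5, -0.5 | 0.0625 / 0.5625 = 11.1% | 90.1% → 93.1% |
| 0.7, -0.7, -0.3 | 0.0361 / 0.2601 = 13.9% | 97.6% → 98.9% |

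Over the whole grid the range is 0% to 14% of residual variance and 0 to 3 power points. In the last row the numerator before squaring is -0.3 + 0.49 = +0.19, so more distress would predict better well-being given baseline MHC-SF. That is an unlikely pattern, and the row marks an outer limit. The baseline mediator items are left out of this calculation; they would probably take up part of the gain.

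**3. Dropout.** Assume baseline HADS = -0.6 × baseline MHC-SF + independent noise (both in SD units), and logit P(respond) = 0.9 + g × HADS, with g allowed to differ by arm. This gives about 70% response in each arm. With HADS omitted,

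bias = β × D,

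where β is the HADS slope given baseline MHC-SF (assumed -0.1 to -0.3), and D is the arm difference in baseline HADS among responders, given baseline MHC-SF. D comes from a simulation of 4 million records.

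| g, control / intervention | D | Bias (SD), β = -0.1 to -0.3 |
|---|---|---|
| -0.5 / -0.5 | 0.00 | 0.00 |
| 0 / -0.5 | -0.09 | 0.009 to 0.027 |
| 0.25 / -0.5 | -0.14 | 0.014 to 0.041 |
| 0.5 / -0.8 | -0.24 | 0.024 to 0.072 |

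A separate simulation with a true effect of 0.30 agrees. Without HADS, the second row gives 0.308 to 0.327 and the third 0.313 to 0.342. With equal dependence the estimate is 0.300 to 0.301. With HADS in the model it is 0.299 to 0.301 throughout.

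**4. What that means for the test.** With residual SD assumed 0.8, the standard error is 0.8 × √(2/176) = 0.085. A bias of 0.01 is 0.12 standard errors and moves a 5% test to about 5.2%. A bias of 0.07 is 0.82 standard errors and moves it to about 13%. As shares of the 0.3 target these are 0.01 / 0.3 = 3% and 0.07 / 0.3 = 23%.

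Steps 2 to 4 use linear models as an approximation to the planned negative binomial regression.

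**The case against.** The strongest reply is that nothing here is wrong. Each model prespecifies the baseline of its own outcome, demographics, and baseline positive thoughts and emotions, which is a sound set for a randomised contrast. That stands.

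Four stronger readings are tempting, and the document supports none of them.

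- **That the omitted scores are shown to predict outcome.** The Background reports that "individuals with poor positive mental health were 7 times more likely to be depressed 10 years later". It does not say this holds given baseline depression, and ten years is not 3 to 12 months. The exclusion criteria also narrow the range of both scales.
- **That dropout bias is present.** It needs two conditions together: HADS predicts outcome beyond the listed covariates, and it relates to response differently by arm. The upper figures in step 3 use opposite-direction dropout, which nothing in the protocol supports. Dropout that depends equally on distress in both arms does no harm here.
- **That the plan ignores the problem.** Complete-case analysis is only the initial approach, and two checks on the missing-at-random assumption follow. A further step may sit in a fuller plan that is not shown.
- **That confounding by distress is left in the mediation models.** The lists belong to the outcome regressions. The article states no covariates for the mediation models and may leave them to the full plan, so no claim is made about them.

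The planned effect-modification tests may bring baseline HADS into some models, but not into the main effect estimate. The word for 'respectively' in the HADS list is also loose, and nothing here turns on whether the other HADS subscale is included.

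What survives the reply is that the lists are stated and are primary, and that they leave out a score already held for every participant.

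**Conclusion.** This is a low-cost improvement, not an error. The planned adjusted models are valid. Adding the other scale would gain about 0 to 3 power points, which would not justify the change by itself. The better reason is insurance: if dropout relates to baseline distress differently by arm, the planned contrast would be off by roughly 0.01 to 0.07 SD, and including the scores brings the bias to about zero. The direction follows the pattern of dropout. The scenarios above, in which the intervention arm loses more distressed students, overstate benefit; the reverse would understate it. All these sizes rest on assumed correlations, slopes and dropout patterns. What rests on the document alone is the omission itself, the availability of both scores before randomisation, the 30% expected non-response, the complete-case start and the open allocation.

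**What to change.** In Statistical Methods, add one sentence to the covariate lists: the adjusted MHC-SF total and subscale models also include baseline HADS depression and anxiety, and the adjusted HADS models also include baseline MHC-SF total.

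The cost is two extra terms in each MHC-SF model and one in each HADS model, on about 352 respondents. No new data are needed, and no covariate values should be missing, because the baseline questionnaire is completed before randomisation. The sample size does not change. The sentence should be fixed before outcomes are compared by arm, since adding HADS after seeing an attrition imbalance would be a post hoc choice.
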